**Methods/Design:**

The study employs a before and after design with a nested exploratory trial of SMBG and r-CGM. A total of 102 insulin naïve T2D patients with a glycated haemoglobin (HbA1c) level of >7.5% in the previous 6 months while treated with maximal oral therapy will be recruited and screened from 22 primary care practices in Melbourne, Australia. All patients will be commenced on a basal insulin regimen following randomization into one of the two blood glucose monitoring arms, with intensification to a “basal plus” regimen if required. The outcomes of the new model of care will be benchmarked with data collected over the same period from a specialist setting in Melbourne, Australia.

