• Having previous or current treatment with insulin (excluding the short term use of insulin in acute illness or during hospitalization).

• On Glucagon-like peptide-1(GLP-1) medication

• Non-English speaking.

• Having vision/cognition/renal function impairment or having major medical/psychiatric illness.

• Having recent or ongoing life-threatening illness.

• Having needle phobia.

• Pregnant or planning to be pregnant.

#### **
*Screening and baseline assessment*
**

At the screening visit and after written consent is obtained, patients will be provided with and will be taught to use the study blood glucose meter which will be provided as well as general diabetes education including foods containing carbohydrates, the importance of regular exercise, brief explanation of progression of T2D and why insulin is now needed, and a blood glucose monitoring record book. Patients will be asked to perform twice daily glucose levels prior to the next appointment. An r-CGM device will be attached to all patients during this visit allowing collection of a week’s r-CGM trace prior to randomization. Patients will then have blood drawn for HbA1c at the local Diabetes Control and Complications Trial (DCCT) aligned pathology provider designated for the study.

Within a week of screening, patients will visit their primary care team for a baseline assessment and enrollment visit. Those with a study HbA1c ≤7.5% will be excluded from the study and will be referred back to usual care. Patients who meet the inclusion and exclusion criteria will be enrolled into the study and will be asked to complete baseline surveys prior to randomization to either self monitoring of blood glucose (SMBG) alone (Freestyle Optium™; Abbott) or with adjunct r-CGM (*i*Pro™2/Enlite™; Medtronic). Randomization will be generated using computerized random number table that will be held by a researcher independent of the study team. Random allocation will be kept in sealed envelopes and randomization will occur prior to the initiation of insulin therapy. Blinding of researchers, practices and patients will not be possible once the random allocation is revealed due to the nature of the study.

#### **
*Self-monitoring arms*
**

• *Self-monitoring of blood glucose with adjunct (r-CGM) arm*

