The power calculation was based on one sample comparison of mean against a reference value. The HbA1c reference value was 8.23% as reported in the INSTIGATE study [4] assuming no change in HbA1c without the intervention. The new model of care was estimated to result in HbA1c reduction of 0.4%. Based on a standard deviation of 1.44 in the FIELD study [30] with a two-sided alpha of 0.05 and 80% power, a sample size of 102 patients is required to detect change in the primary outcome. Our previous research suggests that in an average two full-time-equivalent primary care physician practice we expect to identify 80–100 patients with T2D. Of these we anticipate 10% (8–10) will meet our inclusion criteria and 50% recruitment rate, generating on average 4–5 participating patients per practice. A total of 22 primary care practices will be required. Our sample is not powered to detect change between SMBG and r-CGM but rather to explore the feasibility and efficacy of r-CGM in primary care.

#### **
*Statistical analysis*
**

The primary analysis will be the change in HbA1c based on the entire sample at baseline, 12 and 24 weeks. This analysis will produce a conservative estimate of the benefit of insulin therapy as glycemic control tends to rise without the introduction of insulin in this population. The changes in HbA1c will be benchmarked against those obtained from patients under specialist care who have been initiated on insulin. A secondary analysis will examine the absolute change in HbA1c between the r-CGM and SMBG groups. Comparisons of the entire sample as well as between r-CGM and SMBG will be made at baseline, 12 and 24 weeks for all secondary endpoints.

#### **
*Trial monitoring*
**

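### The 102 patients are the bare one-sample minimum, yet the abstract counts them at screening and nothing is allowed for loss or clustering by practice

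*Protocol article*

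**What the plan says.** All references are to the protocol article.

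- **Basis of the number** (Study procedures, Sample size calculation): the method is given as "The power calculation was based on one sample comparison of mean against a reference value". For the comparator, the section relies on a cited cohort: "The HbA1c reference value was 8.23% as reported in the INSTIGATE study". The assumed benefit is a drop of 0.4 percentage points. The other inputs read "Based on a standard deviation of 1.44 in the FIELD study [30] with a two-sided alpha of 0.05 and 80% power", and from these the authors conclude that "a sample size of 102 patients is required to detect change in the primary outcome".
- **Practices** (same section): an expected yield of 4–5 participants each, and "A total of 22 primary care practices will be required".
- **Stage of counting** (Abstract, Methods/Design): the 102 patients "will be recruited and screened from 22 primary care practices in Melbourne, Australia".
- **Exclusion after screening** (Screening and baseline assessment): "Those with a study HbA1c ≤7.5% will be excluded from the study". This happens at the baseline visit, after consent and screening but before enrolment and randomization.
- **Endpoint and loss**: the primary endpoint is the change in HbA1c from baseline to 24 weeks (Follow-up and endpoint determination procedures). Trial monitoring lists withdrawal criteria, including withdrawal of consent.
- **Clustering**: the intervention is delivered by physician and nurse teams trained within practices (Training in the model of care). Clustering comes up only under Study design issues, as a reason for not cluster-randomizing the monitoring arms. The primary before-and-after comparison is not discussed there.

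No loss rate, ICC or design effect is stated.

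**The concern.** A sample size equal to the formula's minimum delivers its power only if every counted patient contributes an independent 24-week value. The article itself describes three ways in which that fails: the abstract counts patients before a further exclusion, some withdrawals are foreseen, and patients are grouped under practice teams whose skill and discretion are part of what is being tested. Outcomes within a practice are therefore plausibly correlated.

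At stake is the power claimed for the primary outcome. The article disclaims power only for the comparison of the two monitoring arms. For the change in HbA1c it claims 80%, and a reader will judge a null or imprecise result against that figure.

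**Working it through.** **Inputs from the Sample size calculation section:** difference 0.4, SD 1.44, two-sided alpha 0.05, power 80%, one-sample comparison, 102 patients, 22 practices. The reference value of 8.23% cancels out, because only the difference enters the formula.

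**Step 1: reproduce 102.** n = [SD × (z₀.₉₇₅ + z₀.₈₀) / difference]² = (1.44 × 2.8016 / 0.4)² = 101.72, rounded up to 102. The article's figure is reproduced exactly. Power at 102 is 80.1% by the normal approximation and 79.4% by the one-sample t-test, which needs 104 for 80%. The powers below are t-test powers.

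**Step 2: loss or exclusion after counting** (rates assumed; the article gives none).

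| Loss | Analysed (102 × (1 − loss)) | Power |
|---|---|---|
| 10% | 92 | 75% |
| 15% | 87 | 73% |
| 20% | 82 | 70% |

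**Step 3: clustering, all 102 analysed** (ICC assumed). Mean practice size m = 102/22 = 4.64. Design effect = 1 + (m − 1) × ICC; effective n = 102 / design effect.

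| ICC | Design effect | Effective n | Power |
|---|---|---|---|
| 0.01 | 1.04 | 98.4 | 78% |
| 0.05 | 1.18 | 86.3 | 72% |
| 0.10 | 1.36 | 74.8 | 66% |

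**Step 4: 15% loss with ICC 0.05.** With 87 analysed, m = 87/22 = 3.95, the design effect is 1 + 2.95 × 0.05 = 1.148, and effective n = 87/1.148 = 75.8. Power is 66.5%. The change detectable with 80% power is 2.80 × 1.44 / √75.8 = 0.46, against 0.40 planned.

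**Step 5: sensitivity to the meaning of 1.44.** Steps 1 to 4 treat 1.44 as the SD of the within-patient change. If it is a cross-sectional SD, and equal at both times, the SD of change is 1.44 × √[2(1 − r)], where r is the baseline-to-24-week correlation (assumed). At the effective n of 75.8:

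| r | SD of change | Power |
|---|---|---|
| 0.3 | 1.70 | 52% |
| 0.5 | 1.44 | 66.5% |
| 0.7 | 1.12 | 87% |

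**Step 6: what follows if practice were ignored in the analysis.** The true size of a nominal two-sided 5% test is 2 × [1 − Φ(1.96 / √design effect)]. With 102 patients this is 7.1% at ICC 0.05 and 9.3% at ICC 0.10.

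**The case against.** **The count is only loose wording.** The sample size section speaks of participating patients, and the screening section enrols only after the HbA1c exclusion, so 102 was probably meant as enrolled patients. That is a fair reading, and it makes the abstract an editorial correction. It does not touch the absence of any allowance for loss or clustering.

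**The power loss is assumed.** Every loss rate and ICC above is an assumption, so the sizes are illustrative. The direction is not: 102 is the uninflated result, so on the article's inputs any loss or positive ICC takes power below 80%.

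**The SD may hide some slack.** This stands in part. If 1.44 is cross-sectional and r is well above 0.5, the study could keep more than 80% power despite loss and clustering. If r is below 0.5, it does worse. The article does not say which SD it is and claims no such slack.

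**The study is exploratory.** It is described as a phase 2 exploratory trial with feasibility among its aims. That lowers the stakes, but the power claim for the primary outcome remains.

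Three stronger readings are tempting, and the article does not support them:

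- *That the planned analysis treats patients as independent.* The Statistical analysis section names no test or model. Independence is a feature of the sample size formula only, and a separate analysis plan may handle practice.
- *That 22 practices cannot yield 102.* 22 × 4 = 88 and 22 × 5 = 110, and 102/22 = 4.64 lies within 4–5. A midpoint of 99 contradicts nothing.
- *That the share excluded at 7.5% or below can be estimated.* The article gives no HbA1c distribution for patients found by the audit. Any figure would have to combine a mean from one cited study with an SD from another, plus an assumed correlation.

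**Conclusion.** The point holds and should be fixed. The arithmetic behind 102 is correct, but the result is a minimum for independent, fully analysed patients. The abstract attaches it to an earlier stage, and no allowance is made for loss or clustering. With a difference of 0.4 and an SD of change of 1.44, plausible assumptions put power between about 66% and 78% instead of the stated 80%.

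A reader might go further and conclude that the trial is underpowered outright. The article does not support that, because it leaves open whether 1.44 is the SD of change, and that single input moves the combined case from about 52% to about 87%. What is established is that the stated 80% does not follow from the design as described.

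**What to change.** 1. Define 102 as patients enrolled after the confirmatory HbA1c, and correct the abstract to match.
2. State whether 1.44 is the SD of the change or a cross-sectional SD. If cross-sectional, give the assumed correlation.
3. Restate the delivered power or detectable change under a stated loss rate and ICC. For example, if 1.44 is the SD of change, 15% loss and ICC 0.05 give about 66.5% power, or a detectable change of 0.46.
4. Account for practice in the primary HbA1c analysis, for example by a practice random effect with a small-sample correction suited to 22 practices. If a separate analysis plan already does so, a cross-reference is enough.

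The cost is a few sentences and a standard model. No extra patients are needed; the price is a less favourable stated power, unless item 2 shows a smaller SD of change.

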### Study procedures

#### **
*Inclusion criteria and recruitment strategies for primary care practices*
**

Inclusion criteria for primary care practices include:

• The primary care practice employs a PN;

• Primary care physicians and PNs have not previously routinely initiated insulin in their practice.

A list of potential practices in the state of Victoria, Australia will be identified from the primary care practice database at the University of Melbourne and referral network of the study investigators (St Vincent’s Hospital, Werribee Mercy Hospital and Baker-IDI Heart and Diabetes Institute). Recruitment will commence within metropolitan Melbourne. An invitation letter and a study flyer will be mailed to eligible practices. Primary care physicians from eligible practices will be contacted by one of the study investigators. Practices who express an interest in participating will receive an in-practice briefing visit by one of the study team. The purpose of the briefing visit is to explain the study in more detail and to obtain written consent from the primary care physicians and PNs to participate in the study.

#### **
*Inclusion criteria and recruitment strategies for patients*
**

Each consented practice will undertake an audit to identify potential patients with the most recent HbA1c > 7.5% in the last 6 months from their electronic medical records and/or pathology providers. Patients who meet the inclusion and exclusion criteria will be sent a letter by their primary care physicians recalling them for review of their diabetes control. During this review, the need for insulin as one of the treatment options available will be discussed with the patient. Patients will be provided with written study information and will be asked to attend a screening visit with the PN to confirm eligibility to participate.

Each potential patient will be screened by the PN according to the study inclusion criteria:

• Uncomplicated, insulin naïve T2D patients.

• Aged 18–80 years old.

• On maximum tolerated doses which have been stable for at least 3 months of two or more oral hypoglycemic agents (OHAs) or in the opinion of the physician insulin is deemed necessary.

• Willing to self-monitor blood glucose levels at least twice daily.

• Willing to commence insulin.

The study exclusion criteria are:

• Patients with T1D.

• Having satisfactory fasting glucose levels (mean <6.0 mmol/L) with post-prandial hyperglycemia (mean >10 mmol/L).

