**

HbA1c will be collected at baseline, 12 weeks and 24 weeks and analyzed by a DCCT aligned centralized laboratory.

#### **
*Follow-up and endpoint determination procedures*
**

The primary endpoint is the absolute change in HbA1c following insulin initiation at baseline compared with 24 weeks. The secondary endpoints include changes r-CGM time spent in low (<4.0 mmol/L), target (4.0-10.0 mmol/L) and high (>10.0 mmol/L) glucose range at baseline, 12 and 24 weeks; symptomatic hypoglycemia; incidence of severe hypoglycemia (hypoglycemia resulting in loss of consciousness or requiring third party assistance); proportion of patients being prescribed a prandial insulin (glulisine) injection; time to reach target HbA1c ≤7%; proportion of patients achieving an HbA1c ≤7% at 12 and 24 weeks); total insulin dose at 12 weeks and 24 weeks; change in quality of life (ADDQOL and SF-36v2 at 12 weeks and 24 weeks compared with baseline); blood pressure (12 weeks and 24 weeks compared with baseline) and weight change (BMI and waist-to-hip ratio at 12 weeks and 24 weeks compared with baseline).

Endpoints for the sub-study comparing r-CGM with SMBG reflect those described above. In addition, patients and PNs’ acceptability and utility of CGM devices at 24 weeks and total primary health care utilization at 24 weeks will be examined.

#### **
*Benchmark data*
**

The glycemic outcomes reflected by changes in HbA1c following implementation of this new model of care in primary care setting will be benchmarked against observational data collected from all patients with T2D commenced on insulin by private endocrinologists/CDE-RN teams over the same period. Data to be collected from benchmark patients at baseline, 12 weeks and 24 weeks include age, duration of diabetes, the presence of diabetic complications (laser requiring retinopathy, ischemic heart disease, lower limb ulceration or amputation, stroke), the frequency of home blood glucose monitoring, the need for an interpreter, employment status, whether they live alone, hospitalization within the last 12 weeks, current medications and HbA1c. These characteristics will allow a comparison of the demographic, costs and outcomes of those patients with T2D commencing insulin in the specialist centers with those in primary care.

#### **
*Sample size calculation*
**

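### The claim that the uncontrolled before-after HbA1c change is conservative is unsupported: entry selection on HbA1c above 7.5% adds regression to the mean in the opposite direction, and the net bias is unknown

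*Protocol article*

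**What the plan says.** All places are in the protocol article, under Study procedures.

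- **Inclusion criteria and recruitment strategies for patients.** Each practice runs an "audit to identify potential patients with the most recent HbA1c > 7.5% in the last 6 months".
- **Screening and baseline assessment.** At the screening visit, "Patients will then have blood drawn for HbA1c at the local Diabetes Control and Complications Trial (DCCT) aligned pathology provider designated for the study". The baseline visit follows within a week, and "Those with a study HbA1c ≤7.5% will be excluded from the study and will be referred back to usual care".
- **Blood collection and assays.** On measurement times, the plan states: "HbA1c will be collected at baseline, 12 weeks and 24 weeks and analyzed by a DCCT aligned centralized laboratory". No second pre-insulin draw is mentioned there.
- **Follow-up and endpoint determination procedures.** As primary endpoint, the plan takes the within-patient difference in HbA1c between baseline and week 24.
- **Sample size calculation.** A one-sample comparison with a reference HbA1c of 8.23%, "assuming no change in HbA1c without the intervention", an expected reduction of 0.4%, SD 1.44, and 102 patients.
- **Statistical analysis.** On the whole-sample change: "This analysis will produce a conservative estimate of the benefit of insulin therapy as glycemic control tends to rise" when insulin is not introduced.

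The Study design issues section explains that an untreated control group was ruled out on ethical grounds. The specialist benchmark patients also start insulin.

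**The concern.** An uncontrolled change is a conservative measure of benefit only if every bias in it runs against benefit, or if those that do outweigh those that do not. The protocol names one bias, the upward drift of HbA1c without insulin. It does not mention a second one that its own entry rule creates.

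A single HbA1c reading is the patient's underlying level plus within-person variation. Discarding readings at or below 7.5% keeps patients whose reading happened to be high and drops those whose reading happened to be low. If the qualifying reading is also the baseline, the retained baseline lies above the patients' underlying level, and the 24-week value falls back even if nothing is done. That fall counts as improvement.

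Readers are told in effect that the primary result is a lower bound. The study is also meant to inform a definitive trial, and an effect size taken as a lower bound when it is not could leave that trial too small.

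**Working it through.** **1. The plan's own figure.** n = (SD × (z₀.₉₇₅ + z₀.₈₀) / δ)² = (1.44 × 2.8016 / 0.4)² = 101.7, rounded up to 102. The stated sample size reproduces, and nothing below changes it.

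**2. Is the qualifying value the baseline?** The document describes one pre-insulin study draw, at screening. HbA1c is then listed at baseline, 12 and 24 weeks, with no second pre-insulin draw. The screening value is therefore the apparent baseline, but this is inferred.

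**3. Inputs.** From the protocol: threshold 7.5% at both stages, SD 1.44, n = 102, planned effect 0.4. Assumed, because the documents do not give them: source-population mean 8.0 to 8.23, within-person correlation ρ from 0.6 to 0.95, normal exchangeable readings, no treatment effect and no drift. SD 1.44 is taken as the SD of the source population.

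**4. One-stage formula, for orientation.** Expected fall = (1 − ρ) × SD × φ(a) / (1 − Φ(a)), with a = (7.5 − mean) / SD. For mean 8.23, a = −0.507, φ(a) / (1 − Φ(a)) = 0.3508 / 0.6939 = 0.506, and the fall is 0.728 × (1 − ρ): 0.29 at ρ = 0.6, 0.15 at 0.8, 0.07 at 0.9.

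**5. Two-stage selection, as the protocol describes it.** Simulation (millions of draws) of audit, screening and 24-week readings, keeping those with audit and screening both above 7.5%. Mean of screening minus 24 weeks:

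| Source mean (SD 1.44) | ρ 0.6 | 0.7 | 0.8 | 0.9 | 0.95 |
|---|---|---|---|---|---|
| 8.23 | 0.214 | 0.152 | 0.094 | 0.043 | 0.021 |
| 8.0 | 0.248 | 0.176 | 0.108 | 0.051 | 0.024 |

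The result is smaller than in step 4 because the audit has already removed many patients with low underlying levels. As a share of 0.4, ρ 0.6 to 0.8 gives 0.094/0.4 = 24% to 0.248/0.4 = 62%; ρ 0.9 to 0.95 gives 0.021/0.4 = 5% to 0.051/0.4 = 13%.

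**6. Other source populations, ρ 0.6 to 0.8.**
- Mean 9.2, SD 1.44: 0.05 to 0.10.
- Mean 8.23, SD 1.0: 0.05 to 0.12.
- Mean 7.5, SD 1.44: 0.14 to 0.33.
- Mean 7.0, SD 1.44: 0.18 to 0.42.

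**7. Fresh baseline.** If the baseline were a separate draw not used for selection, the same model gives a fall of about 0.00.

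**8. Effect on the test.** With the planned SD, the standard error is 1.44 / √102 = 0.143. The chance of a significant result with no true effect is Φ(fall / 0.143 − 1.96) plus a negligible lower tail. A fall of 0.094 gives about 10% and 0.248 about 41%, against a nominal 5%. For ρ 0.9 to 0.95 it is 5% to 7%. With the simulation's own SD of change (0.88 to 1.22 for ρ 0.6 to 0.8), the range is 19% to 54%.

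**9. Break-even.** If these two biases are the only ones, the protocol's claim holds only when the untreated rise over 24 weeks exceeds the artefact in step 5. The documents give no figure for that rise, and the sample size paragraph sets it at zero.

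**The case against.** **The net sign is not shown.** The simulation sets drift to zero, which is the very reason the protocol gives. An untreated rise of 0.10 to 0.25 over 24 weeks would cancel the artefact in the lower-correlation range. This stands. A reader might infer that the primary result will be inflated on balance; the documents do not support that either.

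**The baseline is not stated to be the screening value.** Screening blood goes to a local designated provider, while the baseline sample is said to be analysed centrally, and the two visits are distinct. This stands as a limit. A separate baseline draw would largely remove the problem, but none is described.

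**The magnitude depends on assumed inputs.** No correlation is given in the documents. Requiring stable maximal oral therapy, or a physician's judgement that insulin is needed, may favour patients whose HbA1c is persistently high. The protocol uses 8.23 as a reference for the study sample; used here as a source mean, it yields an enrolled baseline of about 9.1. This stands, which is why a range is shown.

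**Education and glucose monitoring also start at screening.** It is tempting to call their effect a further bias. They belong to the model of care that the study sets out to evaluate, so their effect is part of the target. What remains is loose wording: the sentence credits insulin therapy with what the whole package does.

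**It is one interpretive sentence in an openly exploratory before-after study.** This stands and lowers the severity. It does not rescue the sentence, which is unconditional and leaves out an opposing bias built into the design.

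**Conclusion.** The statement that the primary analysis will be conservative is unsupported. The entry rule adds a downward change through regression to the mean, opposite in sign to the drift the protocol cites. Neither bias is quantified in the documents, and neither an untreated group nor the insulin-treated benchmark removes the artefact.

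Its size is about 0.09 to 0.25 HbA1c points for correlation 0.6 to 0.8, and 0.02 to 0.05 for 0.9 to 0.95, against the planned 0.4. This rests on a source mean of 8.0 to 8.23, SD 1.44, no drift, and the screening value serving as baseline. The artefact can thus be anything from trivial to more than half of the planned effect. The conclusion is that the lower-bound reading is unproven, not that the result is inflated on balance. The point calls for corrected wording and one sensitivity analysis; it does not undermine the design.

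**What to change.** 1. In the Statistical analysis section, delete the word conservative. Credit the change to the model of care rather than to insulin therapy alone. State that the before-after change includes regression to the mean as well as any untreated drift, and that the net bias is of unknown direction.
2. State whether the screening HbA1c is the baseline value, and reconcile the local provider with the centralized laboratory.
3. Retain the audit and screening HbA1c of everyone screened, including those excluded at 7.5% or below.
4. Beside the raw 24-week change, report a sensitivity estimate corrected for regression to the mean. The model should reflect both truncations at 7.5%, since a single-truncation model does not match the selection described, and should cover a range of within-person correlations.

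**Cost.** Wording, plus one analysis on values already obtained. The correction is approximate: audit values may be up to six months old and may come from various laboratories, and the audit-to-screening change mixes regression to the mean with drift. The headline estimate may look smaller. The sample size and the randomized r-CGM versus SMBG comparison do not change.

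### The randomised r-CGM versus SMBG comparison of HbA1c names absolute change and no baseline covariate; stating baseline adjustment is a free but modest gain in precision

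*Protocol article*

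**What the plan says.** All places are in the protocol article, under Study procedures.

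- Statistical analysis, on the randomised arms: "A secondary analysis will examine the absolute change in HbA1c between the r-CGM and SMBG groups".
- Statistical analysis, on the other outcomes, comparisons "between r-CGM and SMBG will be made at baseline, 12 and 24 weeks for all secondary endpoints".
- Follow-up and endpoint determination procedures: "The primary endpoint is the absolute change in HbA1c following insulin initiation at baseline compared with 24 weeks", and for the nested trial: "Endpoints for the sub-study comparing r-CGM with SMBG reflect those described above".

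No test, model or covariate is named for any of these comparisons. Baseline adjustment is neither planned nor ruled out.

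Under Screening and baseline assessment, blood for HbA1c is drawn at screening, patients at or below 7.5% are excluded, and randomisation follows. Blood collection and assays lists HbA1c at baseline, 12 and 24 weeks. The covariate is therefore already in hand.

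The sample size section says that the sample is not powered for the arm comparison. The Abstract says that the findings will inform a larger randomised trial.

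**The concern.** A difference in mean change subtracts the whole baseline value, as if each extra point of HbA1c at baseline carried through to a full extra point at 24 weeks. When the true slope of follow-up on baseline is below 1, this over-corrects. It adds noise, and it leaves the estimate correlated with any chance difference between the arms at baseline. A linear model with baseline as a covariate estimates the slope instead of fixing it at 1.

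Evaluating r-CGM is the study's declared secondary aim, and the nested trial is meant to inform a larger one. Its estimate and interval will be read by whoever designs that trial, so precision that costs nothing is worth taking.

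**Working it through.** **The plan's own figure.** The article uses a one-sample comparison: "The new model of care was estimated to result in HbA1c reduction of 0.4" percentage points, "Based on a standard deviation of 1.44 in the FIELD study [30"], and "with a two-sided alpha of 0.05 and 80% power, a sample size of 102 patients is required". With n = (SD × (1.960 + 0.842) / 0.4)² = (1.44 × 2.8016 / 0.4)² = 101.72, this gives 102. The figure reproduces, and the present point does not affect it.

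**Inputs for the arm comparison.** The article gives 102 patients and an SD of 1.44. The following are assumed: 1:1 allocation (51 per arm), no dropout, no clustering by practice, 1.44 as the SD of HbA1c at a single visit (the article does not say whether it is that or the SD of change), and a correlation ρ between baseline and 24 weeks of 0.3 to 0.7.

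Half-width of the 95% CI = t(0.975, 100) × SD × √(2/51) = 1.984 × 0.1980 × SD = 0.3929 × SD.

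**Case A: equal SD of 1.44 at both visits.**
- Change score: variance = 2 × 1.44² × (1 − ρ).
- Baseline-adjusted: variance = 1.44² × (1 − ρ²).
- Ratio = (1 + ρ)/2.

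| ρ | SD, change | SD, adjusted | Variance ratio | Half-width | Same precision from change scores needs, per arm |
|---|---|---|---|---|---|
| 0.3 | 1.704 | 1.374 | 0.65 | 0.67 to 0.54 | 51/0.65 = 78 |
| 0.5 | 1.440 | 1.247 | 0.75 | 0.57 to 0.49 | 51/0.75 = 68 |
| 0.7 | 1.115 | 1.028 | 0.85 | 0.44 to 0.40 | 51/0.85 = 60 |

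Simulation of 4,000 trials per ρ gave standard error ratios of 0.81, 0.86 and 0.92, in line with √0.65 = 0.81, √0.75 = 0.87 and √0.85 = 0.92.

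**Case B: baseline narrowed by the entry rule.** Take baseline HbA1c as normal before selection, with mean 8.23 and SD 1.44 (the article's figures, used here as an assumption), and cut it at 7.5. Assume too that the screening value serves as baseline.
- Cut point: a = (7.5 − 8.23)/1.44 = −0.507; λ = φ(a)/(1 − Φ(a)) = 0.506.
- Baseline variance after selection = 1.44² × (1 + aλ − λ²) = 1.012, so the SD is about 1.01.
- Selecting on baseline leaves the slope b (equal to the pre-selection ρ) and the residual variance unchanged. The adjusted variance stays at 1.44² × (1 − ρ²). The change-score variance is that plus (1 − b)² × 1.012.

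| ρ before selection | Adjusted variance | Excess in change score | Variance ratio | Half-width | Per-arm equivalent |
|---|---|---|---|---|---|
| 0.3 | 1.887 | 0.496 | 0.79 | 0.61 to 0.54 | 64 |
| 0.5 | 1.555 | 0.253 | 0.86 | 0.53 to 0.49 | 59 |
| 0.7 | 1.058 | 0.091 | 0.92 | 0.42 to 0.40 | 55 |

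**If 1.44 is the SD of change instead** (equal SDs at both visits), the half-width is 0.3929 × 1.44 = 0.57 unadjusted. Multiplying by √((1 + ρ)/2) gives 0.46, 0.49 and 0.52 at ρ = 0.3, 0.5 and 0.7.

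**Chance imbalance.** The standard error of the baseline difference between arms is 1.44 × √(2/51) = 0.285, so a gap of 0.4 points or more in either direction occurs in about 16% of randomisations. With a baseline SD of 1.0 it is about 4%. At slope 0.5, a gap of 0.4 shifts the change-score difference by (1 − 0.5) × 0.4 = 0.2 points with no effect of r-CGM at all.

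**The case against.** The strongest reply is that the article is silent rather than wrong. Absolute change defines an endpoint, and a model for change with baseline as covariate gives the same treatment estimate and standard error as a model for the 24-week value. The proposed analysis is therefore compatible with the present text, and covariates are commonly left to a fuller plan that is not shown. This stands in part. A reader might infer that the trial is committed to an unadjusted analysis, and the article does not say so. What remains is that it names the between-arm quantity with no covariate while the covariate is already collected.

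Three further inferences are tempting and not supported.

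- **That the entry rule makes change scores perform worse.** Selection above 7.5% does lower the correlation, but it also shrinks the baseline variance and leaves the slope alone. Case B shows that the advantage of adjustment gets smaller.
- **That the plan tests for baseline differences.** The sentence beginning "Comparisons of the entire sample as well as between r-CGM and SMBG will be made at baseline, 12 and 24 weeks" concerns the secondary endpoints and names no test. A descriptive table by arm fits it equally well.
- **That the change-score comparison is biased, or that adjustment rescues its power.** Randomisation makes it unbiased on average either way. With normal quantiles and Case A at ρ = 0.5, power for an illustrative 0.4-point arm difference rises only from 29% to 37%.

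The gain is also not guaranteed. It vanishes if the slope is about 1, for example with baseline SD 1.0, follow-up SD 1.44 and ρ = 0.7, where the slope is 0.7 × 1.44/1.0 = 1.01.

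**Conclusion.** The point holds as a costless improvement to a secondary, exploratory comparison, not as an error in the plan. Over the correlations considered, adjustment lowers the variance of the arm difference by 15% to 35% with equal SDs, and by about 8% to 21% if the entry rule narrows the baseline SD to about 1.0. It also removes the part of the estimate that tracks chance baseline imbalance. Correlation, allocation ratio, dropout and the meaning of the 1.44 are all assumptions, so these are ranges and not predictions. The primary whole-sample analysis and the 102 patients are unaffected, and the arm comparison remains not powered.

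**What to change.** In the Statistical analysis section, state that the r-CGM versus SMBG difference in HbA1c at 24 weeks will be estimated from a linear model with arm and baseline HbA1c, and reported with a 95% CI. The outcome may be the 24-week value or the change; the treatment estimate is the same, so the endpoint definition can stay.

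State that other continuous outcomes (r-CGM time in range, weight measures, blood pressure, quality of life) will be handled the same way, each with its own baseline. State that baseline data by arm will be presented descriptively.

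The cost is a few lines of wording. No new data, visits or patients are needed, since these baselines are already collected.
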